### Participant timeline

#### Recruitment

When the patient meets inclusion criteria, one close relative will be invited to participate in the study. Relatives will be randomized upon written consent and collection of baseline data to reduce the risk of selection bias. Patients will not be approached for the study until they have regained their cognitive abilities—often not occurring until after they are moved to the ward. Patient-relative dyads will be recruited for the interview study at this point, and consent to see the diary will be sought at the first interview, see Fig. 1.

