#### Follow-up

A questionnaire will be mailed to all participants at 3 months post-ICU discharge. A reminder will be mailed 2 weeks later for non-responders to reduce attrition bias. After completion of the questionnaire, two interviews will be conducted at 3–4 months and 7–12 months post-ICU discharge with a smaller group of patients and relatives sampled for the qualitative studies. Patients and relatives will be interviewed as dyads when possible; however, relatives and patients may not be able to be interviewed together due to the late recovery of some patients or the busy schedules of participants, see Fig. 1.

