### Sample size, recruitment and attrition

For the randomized controlled trial, a minimum of 71 patients in each group will be required, assuming a significance level of 5%, a power of 80%, an MCID of 4 points and a median PTSS-14 score of 24 (SD12) [35]. The Danish National Patient Registry of 2014–15 identified 3325 admissions to the study sites, out of which 1016 patients received ventilator treatment. ICU mortality was close to 30%. Based on this, we aim to include 100 patients/relatives pairs in each arm of the study. We estimate that 50% of the mechanically ventilated patients will be eligible for the study, therefore inclusion in the project is estimated to run for 30 months, starting March 2015 (see Fig. 1).

For the qualitative studies, 12 patient-relative dyads who have received the intervention will be sampled among participants in the intervention group. Patient-relative dyads will be selected to achieve phenomenological variation. This sampling strategy aims to achieve variations of experience of the phenomenon rather than variations of specific demographic variables [52]. In practice, we will approach patients and relatives consecutively as each individual has their own unique experience to share. Sampling diaries within the interview group will create strong coherent qualitative data.

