### Randomization and blinding

Relatives will be randomized at a 1:1 ratio to either the intervention group or control group by the investigator or by study nurses using sealed, opaque envelopes. Block randomization ensures that each site randomizes equally to both groups. Because this is not feasible, the investigator, study nurses and participants will not be blinded to group allocation. However, to reduce the risk of detection bias, the investigator will be blinded to group allocation during data entry. The identity of each respondent will be masked and can only be re-identified using a separately kept key-file.

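### The target of 100 pairs per arm allows for ICU deaths only, leaving about 70 expected patients per arm and no margin for refusal, non-response or later death

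*Protocol article*

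**What the plan says.** All of the sizing is in the protocol article, Methods, *Sample size, recruitment and attrition*. It states that "a minimum of 71 patients in each group will be required". The inputs listed for that number are a 5% significance level, 80% power, a difference of 4 points as the minimal important difference, and an SD of 12 on the PTSS-14. It adds that "ICU mortality was close to 30"%, and concludes: "Based on this, we aim to include 100 patients/relatives pairs in each arm of the study". ICU mortality is the only loss to which the section gives a figure, although its heading names attrition.

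Other sections describe further losses on the patient side:

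- *Randomization and blinding*: "Relatives will be randomized at a 1:1 ratio to either the intervention group or control group". *Recruitment* places this after the relative's consent and baseline data. For the patient, the same section says: "Patients will not be approached for the study until they have regained their cognitive abilities". Patient consent therefore comes after allocation.
- *Exclusion criteria* foresees patients who die or decline, and keeps their relatives in the study.
- *Follow-up*: the outcome is a questionnaire sent 3 months after ICU discharge, and "A reminder will be mailed 2 weeks later for non-responders to reduce attrition bias". Some non-response is therefore expected.

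**The concern.** The section gives a minimum, one loss rate and a target said to follow from them. The target roughly equals the minimum divided by the ICU survival fraction, rounded down. A patient contributes PTSS-14 data only after surviving the ICU, living to 3 months, consenting once cognition has returned, and completing the questionnaire. Only the first of these steps is allowed for.

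The patient comparison is the first objective and PTSS-14 is the primary outcome. If the evaluable number falls short, a null result could not exclude the trial's own 4-point minimal important difference, yet it might be read as evidence of no effect. The stated 80% power would encourage that reading.

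**Working it through.** **Inputs.** From *Sample size, recruitment and attrition*: minimum 71 patients per group, significance level 5%, power 80%, difference 4 points, SD 12, ICU mortality about 30%, target 100 pairs per arm. From *Data analysis*: Student's t-test on mean PTSS-14. From *Randomization and blinding*: 1:1 allocation. A two-sided test is assumed, because sidedness is not stated.

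**1. Reproducing the target of 100.** Pairs needed = minimum / (1 − mortality) = 71/0.70 = 101.4, that is 102. The stated 100 lies within two of this, so it is consistent with 71 inflated for ICU mortality alone. An allowance for any other loss would give a larger number.

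**2. Expected survivors from 100 pairs.** 100 × 0.70 = 70, one below 71. The mortality figure is approximate: 29% gives 71, 28% gives 72 and 25% gives 75. If mortality is exactly 30%, the binomial probability that a given arm has at least 71 survivors is 0.46. For both arms it is 0.46² ≈ 0.21.

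**3. Losses after ICU survival.** Evaluable patients = 100 × 0.70 × consent × response. The article gives no consent or response rate, so the range below is an assumption: 10–20% refusal and 10–30% non-response.

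- Low loss: 100 × 0.70 × 0.90 × 0.90 = 56.7
- High loss: 100 × 0.70 × 0.80 × 0.70 = 39.2

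Deaths between ICU discharge and 3 months would lower both figures.

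**4. Power and precision.** Two-sample t-test, standardised difference 4/12 = 0.333, two-sided 5%. Half-width of the 95% CI = t(0.975, 2n − 2) × 12 × √(2/n).

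| Patients per arm | Basis | Power for 4 points | 95% CI half-width | Difference detectable with 80% power |
|---|---|---|---|---|
| 71 | stated minimum | 51% | 1.977 × 2.014 = 4.0 | 5.7 |
| 70 | ICU deaths only | 50% | 1.977 × 2.028 = 4.0 | 5.7 |
| 57 | low assumed loss | 42% | 1.981 × 2.25 = 4.5 | 6.4 |
| 39 | high assumed loss | 31% | 1.992 × 2.71 = 5.4 | 7.7 |

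(The last two rows use 56.7 and 39.2.)

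**5. Separating the two causes.** The stated inputs require 2 × 12² × (1.960 + 0.842)² / 4² ≈ 142 per group, so 71 is about half. That error alone takes power from 80% to about 51%. Attrition takes it from 51% to 50% on documented figures, and to 42–31% on the assumed losses. Attrition therefore adds 0 to 1 point on documented figures, or about 9 to 20 points on assumed ones.

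**6. Relatives.** They remain when the patient dies or declines, so evaluable relatives = 100 × response. With an assumed 80–100% response and the same SD of 12 (also an assumption), power is 55–65% and the half-width 3.7 to 3.3 points (1.975 × 1.897 and 1.972 × 1.697).

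**The case against.** **The gap of 70 against 71 is rounding.** This stands. Seventy is an expected value based on an approximate rate, not a ceiling, and the gap closes at 29% mortality. A reader might infer that the trial cannot have more than 70 patients per arm, or cannot reach 71; the article does not support either. What remains is the absence of margin, which does not depend on one patient.

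**The 30% may not describe the enrolled pairs.** This stands in part. The section does not say whether the rate refers to all admissions or to ventilated patients, and eligibility requires an expected stay of at least 48 h. Some early deaths may also be short-stay exclusions, and excluded pairs might be replaced. For these reasons exclusion for short stay or ventilation is not counted as a further loss above. Refusal, non-response and later death are unaffected.

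**Power below 50% rests on assumed rates.** Correct: documented figures alone give about 50%, and 42–31% holds only under the stated assumptions. The reminder may reduce non-response, but no rate is given.

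**Most of the power deficit belongs to the separate error in the 71.** This stands and is shown in step 5. The two defects need separate corrections: 102 or more pairs would not restore 80% power, and a corrected 142 without an attrition allowance would again fall short (142/0.70 = 203 pairs per arm for ICU deaths alone).

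**One figure serves patients and relatives.** A reader might take the shared 100 as an error. It is not, because recruitment is by pair. The two hypotheses will simply have different evaluable numbers.

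**A condensed article may omit attrition detail.** This has limited force here, because the article states a minimum, one loss rate and a target based on them under a heading that names attrition.

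**Conclusion.** The concern holds as a sample-size assumption without margin. One hundred pairs per arm gives about 70 expected ICU survivors against a stated minimum of 71. Any patient refusal, non-response or death before 3 months takes the expected number below that minimum, and the protocol's own procedures make the first two likely. The design does not deliver 80% power for the patient hypothesis. Power is about 50% on documented figures, mostly through the separate error in the 71. It is about 42% to 31% if 10–20% of survivors refuse and 10–30% do not respond. The arithmetic assumes a two-sided 5% test, SD 12, and that 30% mortality applies to the enrolled pairs. The shortfall against the minimum concerns patients only, since relatives stay in the study after a patient's death or refusal.

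**What to change.** Enrolment need not increase. In *Sample size, recruitment and attrition*:

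1. State the expected evaluable number for patients as 100 × survival × consent × response, and for relatives as 100 × response. Mark the rates as assumptions and give a range.
2. Give the resulting power and 95% CI half-width for each hypothesis, and state the SD assumed for relatives.
3. Do not present 100 pairs per arm as delivering the 71-patient minimum or 80% power for the patient comparison.
4. Correct the 71 itself as a separate item, and use the corrected requirement as the benchmark in this paragraph.

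The cost is a few lines of text. The downside is that the stated figures become less favourable: about 50% power or less for patients, and a half-width of at least 4 points, as large as the difference the trial seeks to detect.

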### Randomization and blinding

Relatives will be randomized at a 1:1 ratio to either the intervention group or control group by the investigator or by study nurses using sealed, opaque envelopes. Block randomization ensures that each site randomizes equally to both groups. Because this is not feasible, the investigator, study nurses and participants will not be blinded to group allocation. However, to reduce the risk of detection bias, the investigator will be blinded to group allocation during data entry. The identity of each respondent will be masked and can only be re-identified using a separately kept key-file.

### Data collection and management

Patient baseline data include date of birth, age, sex, LOS-ICU, hours on ventilator, reason for admission to intensive care (medical/surgical), SAPS-II score [53] and level of education (higher, medium/low or none). Relative baseline data include age, sex, relationship to patient and level of education. Baseline data will be managed using Epidata software.

The primary outcome is measured on the PTSS-14 scale [48] developed for critically ill patients and used in studies evaluating the effect of a nurse-written diary [35, 38] on patients and relatives. The PTSS-14 is an update of the existing PTSS-10 scale based on the DSM-lll criteria, including items related to numbing and re-experiencing corresponding with the DSM-lV [48]. The PTSS-14 has been validated by Twigg et al. [48] in a cohort of patients from general ICUs in the UK. Content validity was assessed by a multidisciplinary group of experts in PTSD [48]. Criterion validity was assessed by comparing the PTSS-14 to the Post-traumatic Stress Diagnostic Scale (PDS), showing good concurrent validity with Pearson’s correlation of 0.86 at 3 months post-ICU discharge [48]. An ROC curve analysis determined 2 months post-ICU as the most favorable time to administer the PTSS-14 (AUC 0.950) [48]. However, for the diary to have time to show an effect, we will administer the PTSS-14 at 3 months (AUC 0.936, sensitivity 100%, specificity 84%) [48]. The PTSS-14 has previously been used in the RACHEL study [35, 38]. For that study [35], the PTSS-14 was translated into Danish. The process of translation involved translation back and forth, but no further validation of the Danish version. The PTSS-14 has been shown to be easy to administer to the fragile population of former ICU patients [48]. However, the fact that it is neither based on the newer DSM-V criteria nor fully validated in Danish poses some limitations. Secondary outcomes are determined by using the HADS [49] and SF-36 [50]. The HADS assesses anxiety and depression. The two scales have moderate-to-strong correlation [54], and optimal balance between sensitivity and specificity is achieved using a cut-off value of 8 for both subscales. This was done by Knowles and Tarrier [37], whereas actual cases are more conservatively estimated using a cutoff value of 11 [55]. Finally, the SF-36 will be used to measure health-related life quality. The SF-36 measures health in 8 domains [50]. Although a newer version exists (SF36 v.2), the original version will be used, as Danish reference values for this version exist [50]. Using scales to assess psychological problems like PTSD, anxiety and depression have the inherent limitation that no actual diagnosis is made; instead, we focus on reducing symptoms. Unfortunately, no general agreement exists on which outcomes to measure in trials regarding interventions to improve rehabilitation for ICU patients [55], so to ensure comparability with other studies, the PTSS-14, HADS and SF36 have been chosen. All inventories are available in Danish. They will be administered at 3 months post-ICU discharge by mail or e-mail (SurveyXact), depending on the choice of each participant. Paper questionnaires will subsequently be entered into SurveyXact by the investigator and pseudonymized.

The photocopied diaries will be transcribed verbatim, noting drawings, changing of pages, underscoring and other non-text elements. Pictures will be described in terms of content.

Interviews will be conducted at the homes of the patients and/or relatives in order to keep relatives and participants as comfortable and safe as possible. Open-ended questions will be used to explore the participants’ experiences of the diary allowing participants to recount these experiences in their own language [56]. The interviews will be digitally recorded and transcribed verbatim. Expressions of feelings will be put in parenthesis (e.g., sounds of laughter, crying, loud or muffled voices) and pauses indicated by ellipses in the transcripts [56].

### Data analysis

From the questionnaires, the total PTSS-14 mean score will be calculated for each group and compared using students’ t-test. If necessary, logarithmic transformation will be undertaken to achieve normality. The two HADS subscales describing anxiety and depression will be analyzed separately. Both subscales will be dichotomized using a cut-off value of 11. The number of cases in each group will be compared using a Chi-square test. The eight domains of the SF-36 will be calculated for each group and compared using Wilcoxon’s rank-sum test. The statistical analysis will be managed using STATA software.

In the analysis of the qualitative data (diaries and interviews) the meaning will be sought through a three-step analytic process, drawing on the interpretation theory of Ricoeur [51]. Thus, the data material will first be read thoroughly to become familiarized with it. A naïve interpretation will be formulated for each interview or diary, representing an overall naïve understanding [51] of the data. The structural analysis within the text will explain the text in terms of its smaller parts, moving from what the text says to what may be understood from the text - its reference to the world [51]. The process of explaining the text in terms of its internal relationships will serve as a validation or modification of the initially formulated naïve interpretation. This will allow the most significant interpretation to stand out in the critical interpretation. Thus, Ricoeurs’ interpretation theory will allow us to move from the specific situation of the participants to a more general and comprehensive understanding of diaries authored by relatives [51].

Subsequently, the findings of the qualitative studies and the results of the RCT will be compared. The extent to which they relate to each other will enable a more comprehensive and nuanced interpretation of the diary intervention to be made.

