### Setting

The study setting is four medical/surgical ICUs at two regional hospitals and one university hospital in Western Denmark. Levels of ICU certification among nurses range from 50 to 60% at the university hospital to more than 90% in the regional hospitals. A list of study sites can be obtained from the first author.

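### The primary PTSS-14 t-test uses neither the site blocking nor the baseline data collected: a modest, avoidable loss of efficiency, not a bias

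*Protocol article*

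**What the plan says.** - **Primary analysis** (Data analysis): a Student's t-test on group means. The text says that "the total PTSS-14 mean score will be calculated for each group and compared using" this test, with a log transformation if normality requires it. No site term or covariate is named.
- **Allocation** (Randomization and blinding): "Relatives will be randomized at a 1:1 ratio to either the intervention group or control group", and "Block randomization ensures that each site randomizes equally to both groups".
- **Sites** (Setting): "four medical/surgical ICUs at two regional hospitals and one university hospital in Western Denmark". ICU certification among nurses is 50 to 60% at the university hospital and above 90% at the regional hospitals.
- **Patient data** (Data collection and management): "Patient baseline data include date of birth, age, sex, LOS-ICU, hours on ventilator". The list goes on to the type of admission (medical or surgical), SAPS-II and education.
- **Relative data** (same section): "Relative baseline data include age, sex, relationship to patient and level of education".
- **Timing**: Recruitment places randomisation after consent and after baseline data are gathered. Inclusion criteria rest on the expected stay and expected ventilation. Under Participant timeline, the diary starts at allocation and guidance runs for the rest of the ICU stay.

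**The concern.** Blocking by site balances the arms within each ICU. If PTSS-14 differs between ICUs, an analysis without site leaves between-site variance in the standard error, although the design has already removed it from the treatment comparison. Site differences are plausible here, because ICU nurses deliver the guidance and their certification levels differ by hospital. In the same way, any prognostic information in age, sex, severity or admission type goes unused. Precision is worth having in this trial because the stated sample size gives less power than the article says.

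A second, smaller matter is the label on two variables. ICU length of stay and hours on ventilator are called baseline, but a patient randomised while still in the ICU has not yet accrued either total.

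**Working it through.** **Inputs from the article (Sample size, recruitment and attrition).** Difference 4 points, SD 12, significance level 5% (taken as two-sided; the article does not say), power 80%, minimum 71 patients per group, target 100 pairs per arm, ICU mortality close to 30%.

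**Inputs the article does not give, assumed here.** The share of PTSS-14 variance explained by covariates (R²) is taken as 0.05 to 0.20, and the site intraclass correlation (ICC) as 0 to 0.10. No pre-randomisation PTSS-14 is described, so the covariates are demographic and severity variables of unknown prognostic strength.

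**Step 1: the article's own figure.** For two groups, n per arm = 2 × SD² × (1.960 + 0.842)² / difference² = 2 × 144 × 7.849 / 16 = 141.3, so 142. Without the factor 2 the result is 70.6, so 71, which is the stated number. At 71 per arm the standard error is 12 × √(2/71) = 2.014. Then 4 / 2.014 − 1.960 = 0.026, and power is Φ(0.026) = 51.0%. The noncentral t gives 50.5% at 71 and 49.9% at 70. With 100 per arm and 30% mortality, 100 × 0.70 = 70 patients per arm remain.

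**Step 2: covariates.** Replace SD by 12 × √(1 − R²) and keep everything else (normal approximation):

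| Assumed R² | Residual SD | Power, 71 per arm | Gain (points) | n per arm for 80% |
|---|---|---|---|---|
| 0 | 12.00 | 51.0% | – | 142 |
| 0.05 | 11.70 | 53.1% | 2.1 | 135 |
| 0.10 | 11.38 | 55.3% | 4.3 | 128 |
| 0.20 | 10.73 | 60.3% | 9.3 | 114 |

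At R² = 0.02 the power is 51.8%, a gain below 1 point. R² would have to reach about 0.5 before 71 per arm gave 80%.

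Relatives stay in the study if the patient dies, so up to 100 per arm may be analysed. If the same difference and SD applied to them, and before non-response, power would be 65.4% unadjusted and 67.7%, 70.0% and 75.0% at R² 0.05, 0.10 and 0.20.

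**Step 3: site alone.** Simulation with 4 sites, 18 per arm in each (72 per arm), total SD 12, 10,000 runs per ICC:

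| Assumed ICC | Type I error, t-test | Power, t-test | Power, site-adjusted |
|---|---|---|---|
| 0 | 5.1% | 51.3% | 51.4% |
| 0.01 | 4.8% | 51.4% | 51.7% |
| 0.02 | 5.0% | 52.0% | 52.6% |
| 0.05 | 4.5% | 51.3% | 52.8% |
| 0.10 | 4.3% | 51.5% | 54.6% |

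The simulation error on a 5% rate is √(0.05 × 0.95 / 10,000) = 0.2 points. The fall below 5% is therefore clear only at ICC 0.05 and 0.10.

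**Step 4: the two labelled variables.** Recruitment puts baseline collection before randomisation. Inclusion criteria show that only expected values are known then. Exclusion criteria remove pairs on realised stay and realised ventilation, so the article itself uses these quantities as later totals. Calling them baseline fits Recruitment only if they mean time up to randomisation, and the article does not say that.

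**The case against.** The best defence is that nothing here is an error. Under 1:1 allocation blocked by site, an unadjusted t-test is valid, and the simulation bears this out. A journal article also commonly leaves covariate sets and sensitivity analyses to an analysis plan, which is not shown. The size of any gain rests on an R² and an ICC that the article does not report. All of that stands, except that silence is not the whole story: the article names the primary test, so the comment is on a stated choice.

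Three stronger readings are tempting, and the document does not support them.

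- A reader might infer that ignoring the blocks inflates false positives. The effect is the reverse, and small.
- A reader might infer that adjustment would rescue the sample size. At R² = 0.20 the requirement is still 114 per arm, against 71 stated.
- A reader might infer from the baseline label that the trial means to adjust for total stay or ventilator hours. No adjusted analysis is planned anywhere in the article, and these variables may serve only to describe the sample or apply the exclusion criteria.

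**Conclusion.** The point holds as one of efficiency. The named primary analysis leaves out the site blocking and all recorded baseline data. It is unbiased, and slightly conservative if site is prognostic. The loss is about 0 to 3 power points for site (ICC 0 to 0.10) and about 2 to 9 points for covariates (R² 0.05 to 0.20) at about 70 per arm. Both ranges depend wholly on those assumptions; if site and covariates carry no information, the gain is nil. The facts about the stated test are certain, but the size of the benefit is not. The sample-size figure is a separate matter that adjustment does not settle.

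The labelling conflict between Recruitment and Data collection and management is real but minor. Its likely consequence is that post-randomisation totals appear in a baseline table.

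**What to change.** 1. **Primary analysis.** Replace the t-test with a linear model of 3-month PTSS-14 on arm and site plus a few pre-specified covariates, fitted separately for patients and relatives. Use the log-transformed score if the existing provision applies. For patients, include age, sex, medical or surgical admission, and SAPS-II if it is scored before randomisation. For relatives, include age, sex and relationship. Report the adjusted difference with its 95% confidence interval, and keep the t-test as a sensitivity analysis.
2. **Labelling.** Reconcile Data collection and management with Recruitment. Report total ICU stay and total ventilator hours as post-randomisation descriptors, and state that they will not be covariates.

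**Cost.** This is mostly wording, because the covariates are already collected. The model must be fixed in advance, the timing of SAPS-II must be confirmed, and a few degrees of freedom are spent. For 142 patients, three site terms and four covariates take the residual degrees of freedom from 140 to 133. If ICU days or ventilator hours before randomisation are wanted as true baseline values, they must be recorded as separate items.

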**Method:**

The intervention consists of a hard-cover notebook that will be given to a close relative to write a diary for the critically ill patient while in the ICU. Guidance will be offered by ICU nurses on how to author the diary. The effect of the intervention will be tested in a two-arm, single-blind, randomized controlled trial, which aims to include 100 patient/relative pairs in each group. The primary outcome studied is symptoms of post-traumatic stress (PTSS-14). Secondary outcomes are scores on anxiety and depression (HADS) and the Medical Outcomes Study Questionnaire Short Form 36 (SF-36). The narrative structure and content of the diary as well as its use will be explored in two qualitative studies.

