## Background

### The complex rehabilitation needs of intensive care patients

ICU treatment often involves a prolonged period of ventilator dependency in a highly technical environment, resulting in a wide range of physical, cognitive and psychological impairments [1, 2]. Although many patients regain their strength within the first year, their quality of life is generally negatively affected [3–5].

Psychological problems include symptoms of post-traumatic stress disorder (PTSD), anxiety and depression. Approximately 20% of ICU survivors have clinically significant PTSD symptoms [6], consisting of re-experiencing symptoms, avoidance symptoms, arousal symptoms and cognitive symptoms [7, 8]. Ehlers and Clark [9] suggest that PTSD is characterized by the disruption of meaningful connections between events. Moreover, risk factors include having frightening or unreal experiences in the ICU [6, 10, 11], whereas accurate memories of intensive care may protect against developing PTSD [11]. The prevalence of clinically significant levels of anxiety in ICU survivors is reported to be 6.9–18% [12], and the prevalence of depression is reported to be 28% [13]. Furthermore, 50% of patients surviving critical illness do not return to school or work 1 year post-ICU [14], and impairments have a substantial effect on patients’ and their partners’ financial situations [15].

A key part of restoring quality of life after critical illness is the need to understand what has happened and why it happened. This can be difficult, as memories of intensive care may be absent, incomplete or extremely disturbed due to the critical illness and the use of sedatives. However, research show that patients continuously strive to make sense of their ICU experience [16].

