### Outcomes

The primary measure of outcomes in the randomized controlled trial is the *Post-traumatic Stress Symptoms-14 inventory* (PTSS-14) [48]. Secondary outcomes are measured by scores on the *Hospital Anxiety and Depression Scale* (HADS) [49] and the *Medical Outcomes Study Questionnaire Short Form* (SF-36) [50]. The qualitative studies focus on the meaning that the diary holds to relatives and patients as well as describing the structure and content of the diaries [51].

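### HADS scores are declared as secondary outcomes, but the only stated HADS analysis compares case counts at a cut-off of 11, at a material cost in information and power

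*Protocol article*

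**What the plan says.** The abstract and the Outcomes section of the protocol article both define the HADS outcomes as scores. The Outcomes section reads: "Secondary outcomes are measured by scores on the" HADS and SF-36.

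The Data analysis section takes the two HADS subscales separately and then states: "Both subscales will be dichotomized using a cut-off value of 11". It continues: "The number of cases in each group will be compared using a Chi-square test". No comparison of HADS scores is given. In the same paragraph, PTSS-14 totals are compared by t-test and the SF-36 domains by rank-sum test.

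Data collection and management discusses both cut-offs. On the lower one it says "optimal balance between sensitivity and specificity is achieved using a cut-off value of 8 for both subscales", and it adds that an earlier diary trial used it. On the higher one it says "actual cases are more conservatively estimated using a cutoff value of 11". Of the psychological scales in general it says that "no actual diagnosis is made; instead, we focus on reducing symptoms".

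**The concern.** The variable declared as the outcome is not the variable analysed. HADS is the only one of the three instruments treated in this way.

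A count at 11 registers a change only when a participant crosses 11. A shift that lies wholly below or wholly above that point leaves the count unchanged, although it is a change in symptoms. The Discussion names effects on anxiety and depression, in patients and in relatives, as part of the objective. If a real shift in scores is tested only through a tail count in a trial of this size, it may well be reported as no difference.

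The cut-off that the article itself calls the best balance, and that an earlier diary trial used, appears in no analysis, not even a supportive one.

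**Working it through.** The article gives no power figure for HADS, so there is none to reproduce. The question is how much the dichotomy costs.

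**Inputs from the article**
- Patients (Background, rehabilitation needs of intensive care patients): anxiety 6.9% to 18%, depression 28%.
- Relatives (Background, needs of relatives): depression median 23% (range 8% to 42%), anxiety median 40% (range 21% to 56%).
- Planned size: 100 pairs per arm, with ICU mortality near 30% (Sample size, recruitment and attrition). Surviving patients per arm: 100 × (1 − 0.30) = 70, before any non-response. Relatives stay in the study if the patient dies (Exclusion criteria), so their number may be nearer 100.
- Significance level 5%.

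**Assumptions that are not in the article**
- Scores are roughly normal.
- The prevalences apply at the cut-off used; neither Background section names an instrument or a cut-off.
- Tests are two-sided.
- The illustrative effect is a halving of prevalence.

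**Step 1: information kept.** For a small shift, a cut with proportion p above it keeps E = φ(z)² / [p(1 − p)], where z = Φ⁻¹(1 − p). At p = 0.18, z = 0.915 and φ(z) = 0.2624, so E = 0.0689 / 0.1476 = 0.47 and the loss is 53%.

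| Group and outcome | p | Kept | Lost |
|---|---|---|---|
| Patients, anxiety (low) | 6.9% | 27% | 73% |
| Patients, anxiety (high) | 18% | 47% | 53% |
| Patients, depression | 28% | 56% | 44% |
| Relatives, depression (low) | 8% | 30% | 70% |
| Relatives, depression (median) | 23% | 52% | 48% |
| Relatives, depression (high) | 42% | 63% | 37% |
| Relatives, anxiety (low) | 21% | 50% | 50% |
| Relatives, anxiety (median) | 40% | 62% | 38% |
| Relatives, anxiety (high) | 56% | 63% | 37% |

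The loss reaches half only when p is about 21% or lower. The smallest possible loss, with the cut at the median, is 36%.

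**Step 2: power for a halving of prevalence.**
- Cases: power = Φ{(|p₁ − p₂| − 1.96 × SE₀) / SE₁}, with SE₀ = √[2p̄(1 − p̄)/n] and SE₁ = √{[p₁(1 − p₁) + p₂(1 − p₂)]/n}. For 18% to 9% with n = 70: p̄ = 0.135, SE₀ = 0.0578, SE₁ = 0.0573, (0.09 − 0.1132) / 0.0573 = −0.405, power 34%.
- Scores: the same change as a normal shift is d = Φ⁻¹(1 − p₂) − Φ⁻¹(1 − p₁). For 18% to 9%, d = 1.341 − 0.915, or 0.425 SD before rounding. The noncentrality is 0.425 × √(70/2) = 2.52, and the two-sample t-test has power 71%.

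| Change in prevalence | d (SD) | 70 per arm: cases vs scores | 100 per arm: cases vs scores |
|---|---|---|---|
| 18% to 9% | 0.43 | 34% vs 71% | 46% vs 85% |
| 28% to 14% | 0.50 | 53% vs 83% | 68% vs 94% |
| 40% to 20% | 0.59 | 74% vs 93% | 88% vs 99% |

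**Step 3: 11 against 8.** The article gives no HADS means or SDs. With assumed means of 4 to 7 and SDs of 3.5 to 4.5, and cuts at 10.5 and 7.5 for continuity, the loss is 49% to 84% at 11 and 37% to 56% at 8. This is an illustration only.

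**The case against.** The strongest reply is that 11 is a deliberate choice. The article weighs 8 against 11 and gives a short reason for 11, with a citation. Preferring specificity is legitimate, and fixing one cut-off in advance prevents a later choice between two. This stands: a reader might infer that the cut-off of 8 was ignored, and the text does not support that. But the reason given is for 11 over 8, not for counting cases in place of comparing scores.

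Case counts also help comparison with earlier work, since the Background reports the smaller diary trial in terms of cases. That supports keeping a case analysis. It also supports adding 8, because the article says that this trial used 8.

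The remark about symptoms contrasts scales with clinical diagnosis and does not rule out case counts. That is fair, so the mismatch rests mainly on the declared outcome.

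Three stronger readings are tempting but not supported:
- *At least half of the information is always lost.* This holds only at prevalences of about 21% or lower; for relatives' anxiety at the median the loss is 38%.
- *The HADS comparisons are nearly uninformative.* Halving relatives' anxiety from 40% still has 74% power on cases at 70 per arm, and 88% at 100.
- *Chi-square is invalid here.* For the prevalences checked, the expected cases per arm fall below 5 only with the lowest patient anxiety figure, an assumed halving and about 70 per arm: 70 × (0.069 + 0.0345)/2 = 3.6. At 100 per arm it is 5.2, and at 18% with 70 per arm it is 9.5. Sparse-cell handling is routine detail that an article may leave out.

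Finally, an article may leave detail to a fuller plan. Here, however, it fixes a specific analysis of a different variable from the one declared, which is more than an omission.

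**Conclusion.** The point holds as a mismatch between declared outcome and stated analysis, with a material but variable cost: about 37% to 73% of the information over the article's prevalences. The cost is largest for patients' anxiety and smallest for relatives' anxiety. In the two patient scenarios at 70 per arm, power falls by 37 points (71 − 34) and 30 points (83 − 53); for relatives from 40% it falls by 19 points (93 − 74).

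The percentages are indicative. They rest on a normal model for a bounded and possibly skewed score, on prevalences that the article does not tie to a cut-off of 11, and on an assumed halving. If the prevalences came from a lower cut-off, fewer participants would lie above 11. The loss would then generally be larger, apart from figures above 50%, where it could first dip slightly towards the 36% minimum.

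HADS is secondary, nothing is powered on it, and the primary PTSS-14 analysis is unaffected. The change should be made, but it does not threaten the trial's main conclusion.

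**What to change.** In Data analysis, make a between-arm comparison of HADS-A and HADS-D scores the main HADS analysis, separately for patients and relatives. Report the mean difference with a 95% confidence interval, or use the rank-sum test if the scores are clearly skewed, in line with the methods already named for PTSS-14 and SF-36.

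Keep the count of cases at 11 as a supportive analysis. Add the count at 8 beside it, since the article calls that cut-off the best balance and says that an earlier diary trial used it. State in advance that both counts are supportive, so that neither can be promoted after the results are known.

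The cost is a few sentences. The scores are already collected, so no new data and no change in sample size are needed.
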